## Abstract

**Background:**

As the management of type 2 diabetes remains suboptimal in primary care, the Road to Hierarchical Diabetes Management at Primary Care (ROADMAP) study was designed and conducted in diverse primary care settings to test the effectiveness of a three-tiered diabetes management model of care in China.

**Objective:**

This paper aims to predetermine the detailed analytical methods for the ROADMAP study before the database lock to reduce potential bias and facilitate transparent analyses.

**Methods:**

The ROADMAP study adopts a community-based, cluster randomized controlled trial design that compares the effectiveness of a tiered diabetes management model on diabetes control with usual care among patients with diabetes over a 1-year study period. The primary outcome is the control rate of glycated hemoglobin (HbA_1c_) <7% at 1 year. Secondary outcomes include the control rates of ABC (HbA_1c_, blood pressure, and low-density lipoprotein cholesterol [LDL-C], individual and combined) and fasting blood glucose, and the change in each outcome. The primary analysis will be the log-binomial regression with generalized estimating equation (GEE), which accounts for the clustering within communities, for binary outcomes and linear regression with GEE for continuous outcomes. For both, the baseline value of the analyzed outcome will be the covariate. The other covariate further adjusted models and the repetitive models after multiple imputation (when more than 10% of observations in HbA_1c_ after 1 year are missing) will be used for sensitivity analysis. Five prespecified subgroup analyses have also been planned to explore the heterogeneity of the intervention effects by adding the subgroup variable and its interaction with the intervention to the primary model.

**Results:**

This plan has been finalized, approved, and signed off by the principle investigator, co-principle investigator, and lead statisticians as of November 22, 2019, and made public on the institutional website without any knowledge of intervention allocation. Templates for the main figure and tables are presented.

**Conclusions:**

This statistical analysis protocol was developed for the main results of the ROADMAP study by authors blinded to group allocation and with no access to study data, which will guarantee the transparency and reduce potential bias during statistical analysis.

**Trial Registration:**

Chinese Clinical Trial Registry ChiCTR-IOC-17011325; https://tinyurl.com/ybpr9xrq

**International Registered Report Identifier (IRRID):**

DERR1-10.2196/18333

## Introduction

### Study Background

Being home to the largest diabetic population, China has been encountering challenges in managing diabetes adequately in primary care [1-3]. Currently, patients with type 2 diabetes (T2D) are entitled to four or more yearly free blood glucose tests and treatment consultations at primary care clinics through a publicly funded essential public health service package [4]. Despite the provision of the universal access and increasing subsidies to community health care services [4,5], outcomes of the current management remain suboptimal. It has been reported that among service recipients only 40% have reached the adequate blood glucose control target (glycated hemoglobin [HbA_1c_] <7.0%) [6], while less than a tenth have achieved optimal control of composite cardiometabolic “ABC” (HbA_1c_, blood pressure [BP], and low-density lipoprotein cholesterol [LDL-C]) targets [7]. In July 2017, a cluster randomized controlled trial, Road to Hierarchical Diabetes Management at Primary Care (ROADMAP) study, was launched to determine the effectiveness of a strengthened version of the previously mentioned essential public health service on diabetes management through a mobile health–based, tiered service-delivery intervention in diverse primary care settings in China.

### Study Overview

The ROADMAP study is designed as a community-based, cluster randomized controlled trial, aiming to compare the effectiveness of a hierarchical diabetes management intervention to usual care on blood glucose control. The usual care is the routine diabetes and hypertension management required by the national essential public health service. [4] The intervention delivery is performed by contracted service teams; each of them are composed of one primary care doctor at the community or village level as team leader, one township hospital doctor, and one district or county doctor. The intervention lasted for 1 year. This study is prospectively registered (ChiCTR-IOC-17011325) and ethically approved. A complete study description has been published elsewhere [8].

### Participant Recruitment and Randomization

Participants are adult patients with established T2D who have registered for the essential public health service within the community at the time of recruitment. To be eligible, participants were 18-75 years old, resided in the community for the previous 6 months with no plan of relocating, and provided informed consent. Potential participants were excluded if they had severe physical or psychological injury or illness, were unable to attend the site visit or consciously answer questions, were women in the process of or planning for pregnancy or breastfeeding, or had participated in any other clinical trial within the previous 6 months.

The trial recruited a total of 19,601 participants from 864 communities or villages in 144 districts or counties in 25 provinces. Generally, for each participating province, 6 districts and 6 of its subordinate communities from each district were selected. The same principle applied to counties and villages in rural areas. Following the completion of baseline assessments, communities or villages (clusters) were centrally randomized.

### Intervention

Besides a standard training workshop for the contracted service providers (community, township, and county level doctors) in the intervention arm, the key components of intervention were one BP measurement and two blood glucose monitoring tests (at least one fasting blood glucose [FBG]) monthly, instruction for lifestyle change and medication accordingly, timely referral if an indicator is present, and quarterly performance review for the contracted service team. A mobile health–based information system, Graded ROADMAP, was developed and employed to support the contracted doctor team delivering the intervention. Another smartphone app, Your Doctor, was available for participants in the intervention arm to facilitate health education and communication between the designated doctors and patients. The use of Your Doctor depended on participants’ willingness and capability of using the smartphone app. At the end of this study, all the participants in the intervention arm were divided into two subgroups based on the actual use of Your Doctor: a basic intervention subgroup in which participants have logged in less than 4 times to the app throughout the 1-year follow-up and an intensive intervention subgroup in which the participants have at least 4 log-ins within 1 year.

### Outcomes

The primary outcome is the HbA_1c_ control rate (percentage of patients achieving HbA_1c_ <7.0%; target A) at 1 year. The secondary outcomes include the percentage of patients achieving both systolic blood pressure <140 mmHg and diastolic blood pressure <80 mmHg (target B); the percentage of patients achieving LDL-C <2.6 mmol/L (target C); the optimal control rate of the combined ABC targets as previously defined; the percentage of patients achieving FBG <7.0 mmol/L; the changes in levels of HbA_1c_, BP, LDL-C, and FBG; and the subtype-specific and overall hypoglycemia episodes [9]. Other outcomes are health-related quality of life measured by the EuroQol questionnaire EQ-5D-3L (3-level version of EQ-5D) [10,11], the mean change in the scores of the summary of diabetes self-care activities questionnaire [12], the development of any self-reported onset of new comorbidities and diabetic complications during follow-up, concomitant medications, and direct medical cost.

### Sample Size

A sample size of 16,416 participants (19 patients per community) at 1 year provided an 89% power (2-sided α=.05) to detect a ≥5% absolute increase in the primary outcome for the intervention group. The sample size calculation assumes that 40% of participants will have well-controlled HbA_1c_ levels (<7%) at the end of the study in the control group [6], with an intraclass correlation coefficient of 0.15 based on our previous Observational Registry of Basal Insulin Treatment (ORBIT) study [13]. Furthermore, assuming that 50% of participants (ie, 576 clusters with a smaller average cluster size of 9-10 participants) in the intervention group will receive the intensive intervention (at the patients’ discretion), it will need 93% to detect absolute increases of 5% HbA_1c_ control, when compared to the basic intervention group (576 clusters with an average cluster size of 9-10 patients). Accounting for a potential loss to follow-up of 14% of patients, the study aimed to recruit 19,008 patients with T2D from 864 communities or villages (576 in intervention and 288 in control, with a 2:1 ratio) in 24 provinces in mainland China, which equates to an average of 22 patients from each community or village.

### Objectives

The purpose of this study is to outline the predetermined analytical methods in detail before completion of the database lock to reduce the potential bias and facilitate transparent analyses.

## Methods

### Patient Disposition

The flow of patients through the study will be displayed in a CONSORT (Consolidated Standards of Reporting Trials) diagram (figure shell is shown in Figure 1).

**Figure 1 figure1:**
[figure not shown]
CONSORT diagram for the randomized control trial. BP: blood pressure; EOS: end of study; FBG: fasting blood glucose; HbA_1c_: glycated hemoglobin; ITT: intention-to-treat; LDL-C: low-density lipoprotein cholesterol.

### Population for Analysis

The main analysis will be performed at the patient level following an intention-to-treat (ITT) principle (ie, patients and clusters will be included for analysis as their assigned group, regardless of treatment adherence). All randomized patients that have given consent and are not missing key variables (including gender, age, and HbA_1c_ level) at the baseline assessment will form the ITT population.

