### General Analysis Principles

Analyses will adjust for clustering at the village level. The intracluster correlation coefficients will be calculated and tabulated. The primary comparison will be made between the intervention population and the usual care population. As a secondary comparison, the effects of the intensive intervention (no less than 4 logins to the Your Doctor app in addition to the basic intervention) will be explored by estimating the effects of intensive intervention vs basic intervention. No formal interim analysis will be performed. The primary analysis will use all available data with no imputation. Imputation will be performed as a sensitivity analysis when missing observations in HbA_1c_ levels after 1 year exceed 10%.

Hypothesis tests will be 2-tailed with a 5% significance level maintained throughout the analyses. No adjustment will be applied for multiplicity, given that most of the effectiveness outcomes are correlated or consist in different versions of common variables. Outcomes will be presented in order of their priority (primary vs secondary), and only a limited number of subgroup analyses are prespecified. Subgroup analyses will be carried out irrespective of whether a significant treatment effect on the primary outcome is observed. Analyses will be performed in SAS, version 9.4 or later (SAS Institute).

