#### Imputed Data Analyses

Multiple imputation using fully conditional specification [15] will be performed as a sensitivity analysis when more than 10% of observations in HbA_1c_ is missing at 1 year. The imputation model will include the levels of HbA_1c_, FBG, BP, and LDL-C at 1 year and at baseline; a cluster indicator; a group indicator; and other baseline variables including age, sex, education, duration of diabetes, comorbidities, economic development level, and locality (urban or rural). Ten sets of imputed data will be created and analyzed using the model 1 (described in “Primary Analyses”). HbA_1c_, FBG, BP, and LDL-C will first be imputed as continuous variables using linear regression and subsequently converted into binary variables. Estimates of the intervention effect after imputation (β in model 1) and its standard errors will be combined to obtain a pooled common RR and 95% CI.

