#### Analysis of Hypoglycemia

Episodes of hypoglycemia (each subtype and overall) will be analyzed with the same approach as before; this time using Poisson regression adjusted for the baseline count of hypoglycemia. The effect of the intervention will be estimated as the incidence rate of hypoglycemia episodes and its 95% CI. The number of patients experiencing at least one hypoglycemia episode and the total number of episodes will be tabulated by group. Adjusted analysis and subgroup analysis will also be conducted. No imputation will be performed on hypoglycemia.

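### The set labelled ITT drops randomised patients who lack baseline gender, age or HbA1c, although no primary model uses age or gender and only the HbA1c models use baseline HbA1c

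*SAP article*

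**What the plan says.** Population for Analysis states the ITT principle in the usual way: "patients and clusters will be included for analysis as their assigned group, regardless of treatment adherence". The next sentence narrows the set to "All randomized patients that have given consent and are not missing key variables (including gender, age, and HbA_1c_ level) at the baseline assessment", and these patients "will form the ITT population". No other population is defined for comparing the arms. The word introducing the three variables makes them examples, so the list can grow.

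General Analysis Principles adds: "The primary analysis will use all available data with no imputation". The abstract describes the primary analysis as log-binomial regression with GEE "for binary outcomes and linear regression with GEE for continuous outcomes", so that phrase is not obviously confined to HbA1c.

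On timing, Participant Recruitment and Randomization says: "Following the completion of baseline assessments, communities or villages (clusters) were centrally randomized". On imputation, the sensitivity model is described thus: "The imputation model will include the levels of HbA_1c_, FBG, BP, and LDL-C at 1 year and at baseline". Age and sex are among its other predictors.

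**The concern.** A reader takes ITT to mean that everyone randomised is in the set and that losses come only from missing outcomes. Here a patient can have a complete record for blood pressure, LDL-C and hypoglycaemia and still be absent from all three analyses because a baseline HbA1c result is missing. Hypoglycaemia is a safety outcome, and its model is specified as "this time using Poisson regression adjusted for the baseline count of hypoglycemia", so it makes no use of the field that triggers the exclusion.

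The same patients are removed before multiple imputation. That model already contains baseline HbA1c, age and sex and could retain them, so the imputed analysis cannot show whether the exclusion matters. Because the list is open, a further variable could be treated as key later without departing from the text.

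**Working it through.** **Step 1. Which models use the excluded-on variables?**

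| Model 1 analyses | Number | Baseline covariate | Where stated |
|---|---|---|---|
| HbA1c <7% | 1 | HbA1c | Primary Analyses |
| Change in HbA1c | 1 | HbA1c | Analysis for Continuous Outcomes; Table 3 note a |
| FBG and LDL-C control | 2 | own baseline | Analysis for Binary Categorical Outcomes |
| BP control | 1 | systolic BP only | Table 2 note f |
| Composite ABC control | 1 | none | Table 2 note i |
| Change in FBG, systolic BP, diastolic BP, LDL-C | 4 | own baseline | Table 3 note a |
| Hypoglycaemia, four subtypes and overall | 5 | own baseline count | Analysis of Hypoglycemia; Table 4 note b |
| EQ-5D index and VAS | 2 | own baseline | EQ-5D |
| Self-care score (counted once) | 1 | own baseline | Summary of Diabetes Self-Care Activities |

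That is about 18 analyses. Baseline HbA1c is needed in 2, and age or gender in 0. A patient lacking only baseline HbA1c is excluded from about 18 − 2 = 16 analyses that do not use it. A patient lacking only age or gender is excluded from all 18, none of which uses those fields.

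Elsewhere, age and sex are named for the imputation model and for the propensity score comparing intensive with basic intervention. Age also defines one subgroup. Either could enter model 2 only through the P<.01 baseline screen.

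**Step 2. Reproduce the plan's power.** Inputs from Sample Size: 576 and 288 communities, m = 19 per community (864 × 19 = 16,416), ICC ρ = 0.15, 40% v 45%, two-sided α = 0.05.

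- Design effect: 1 + (19 − 1) × 0.15 = 3.70.
- Patients: 576 × 19 = 10,944 and 288 × 19 = 5,472.
- SE = √[3.70 × (0.45 × 0.55/10,944 + 0.40 × 0.60/5,472)] = 0.01568.
- Power = Φ(0.05/0.01568 − 1.96) = 89.0%; the pooled-variance version gives 88.8%. The stated 89% reproduces.

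**Step 3. Effect of excluding a fraction f scattered across communities.** The plan gives no missing-baseline rate, so f = 1-10% is assumed. Average community size becomes 19(1 − f), and the SE rises by the factor √{[1 + (19(1 − f) − 1)ρ] / [(1 − f)(1 + 18ρ)]}.

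| f | Of 19,601 recruited | Mean size | Design effect | CI wider by | Power (pooled) |
|---|---|---|---|---|---|
| 0 | 0 | 19 | 3.700 | – | 88.8% |
| 1% | 196 | 18.81 | 3.6715 | 0.12% | 88.7% |
| 2% | 392 | 18.62 | 3.643 | 0.23% | 88.7% |
| 5% | 980 | 18.05 | 3.5575 | 0.60% | 88.4% |
| 10% | 1,960 | 17.10 | 3.415 | 1.27% | 88.0% |

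The widening factor depends on m, f and ρ, not on the event rates, so it carries over to another outcome with the same ICC. ICCs for the other outcomes are not given. With a smaller ICC the widening is larger, up to 1/√(1 − f) at ρ = 0, which is 0.5% at f = 1% and 5.4% at f = 10%. The power column refers to the primary outcome and only shows scale.

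**Step 4. What deleting the clause recovers.** For the two HbA1c outcomes, model 1 adjusts for baseline HbA1c with nothing imputed, so patients lacking it drop out whatever the population definition says. Deleting the clause recovers no such patient there. The avoidable loss lies in the other analyses, plus any patient missing only age or gender.

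**The case against.** The best defence is that one common set across the main, model 2, subgroup, propensity-score and imputed analyses is a recognised convention, and that all three variables are used somewhere among them. The section speaks of the main analysis, so its reach to every outcome is inferred from there being no other set. Age 18-75 is an entry criterion and gender is simple to record, so few exclusions are likely on those two; HbA1c is the variable that matters. All of this stands and keeps the point small. It does not explain why models that ignore a variable should require it, or why the result is called ITT.

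Four stronger readings are tempting and are not supported.

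- **Biased comparison.** Baseline was completed before communities were allocated, so missing baseline data should not depend on arm.
- **Consent clause used to remove later withdrawals.** The plan makes consent an eligibility condition and says it was signed before recruitment. The clause most naturally restates that, and someone who withdraws later has still given consent.
- **Contradiction with the all-available-data rule.** That sentence contrasts observed data with imputation and can be read as applying within the defined set. It is a tension only.
- **Loss of whole communities through failed sample batches.** That would take unpooled power from 89.0% to 85.6% at 10% loss, but the plan mentions no such failure. The figure is also for the primary outcome, where model 1 would lose those patients anyway.

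**Conclusion.** The point holds in a limited form. The only defined analysis set is labelled ITT but excludes randomised patients on baseline fields that about 16 of some 18 model 1 analyses do not use, and the list of fields is open. The consequences are discarded outcome data, an imputed analysis that cannot recover these patients, and a label that misdescribes the set.

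The size is small: confidence intervals about 0.1-1.3% wider, with primary-outcome power still about 88% in the worst case considered. This assumes 1-10% missing, scattered loss, ICC 0.15 and 19 patients per community. The missing rate is not in the plan, and a lower ICC for a secondary outcome would raise the widening. No bias in the randomised comparison follows. The change is worth making because it is cheap and the population definition underlies every result.

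**What to change.** In Population for Analysis, define ITT as all enrolled, consented patients in randomised communities, analysed as assigned, and delete the requirement for non-missing baseline variables. State that each model requires only the 1-year outcome and the baseline covariate it uses. State that the imputation step, where it applies, starts from this full set. Keep the present set as a sensitivity analysis under the name modified ITT, with a closed list of required variables and the number excluded reported by arm.

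Optionally, to retain patients whose adjusting baseline value is missing (including baseline HbA1c in the HbA1c models), fill it with the mean pooled over both arms, computed blind to arm, and add a missing-value indicator. Because baseline precedes randomisation, the indicator cannot be affected by allocation. If this is adopted, the no-imputation wording in General Analysis Principles must be amended to refer to outcomes; otherwise the fill contradicts it.

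The cost is a few sentences and a few lines of code, with no new data. Patient numbers will differ slightly between outcomes, and the fill adds one term to the affected models.

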### General Analysis Principles

Analyses will adjust for clustering at the village level. The intracluster correlation coefficients will be calculated and tabulated. The primary comparison will be made between the intervention population and the usual care population. As a secondary comparison, the effects of the intensive intervention (no less than 4 logins to the Your Doctor app in addition to the basic intervention) will be explored by estimating the effects of intensive intervention vs basic intervention. No formal interim analysis will be performed. The primary analysis will use all available data with no imputation. Imputation will be performed as a sensitivity analysis when missing observations in HbA_1c_ levels after 1 year exceed 10%.

Hypothesis tests will be 2-tailed with a 5% significance level maintained throughout the analyses. No adjustment will be applied for multiplicity, given that most of the effectiveness outcomes are correlated or consist in different versions of common variables. Outcomes will be presented in order of their priority (primary vs secondary), and only a limited number of subgroup analyses are prespecified. Subgroup analyses will be carried out irrespective of whether a significant treatment effect on the primary outcome is observed. Analyses will be performed in SAS, version 9.4 or later (SAS Institute).

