### Patient Characteristics and Baseline Comparison

Discrete baseline variables will be summarized by frequencies and percentages. Percentages will be calculated using the number of patients for whom data is available. Continuous variables will be summarized by using mean and SD, and median and interquartile range (Q1-Q3). No adjustment for clustering will be applied when comparing baseline characteristics. Standardized differences between groups in baseline characteristics will be reported. A less than 0.1 standard difference will be used to indicate a negligible difference in the mean or proportion of a baseline variable between treatment groups [14].

Variables for baseline measures will be tabulated, including demographic (age, sex, ethnicity), socioeconomic status (education level, household income, health insurance), anthropometric measurements (weight, BMI, waist circumference, BP), smoking status, diabetic complications, laboratory data (HbA_1c_, FBG, LDL-C, serum creatinine), and score of the summary of diabetes self-care activities.

Cluster characteristics will be summarized in stratified and overall randomization groups. The cluster characteristics at baseline are age of the community or village doctors, smartphone operation system (iOS or Android) that the community or village doctors were using, and number of patients with T2D registered.

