#### Covariates-Adjusted Analyses

The primary model (model 1) previously described will be rerun after further adjusting for the following covariates (model 2): economic development level; locality; and other baseline covariates that have shown a significant difference (*P*<.01) between the intervention and control groups in a univariate comparison, including all the baseline variables previously listed (see “Patient Characteristics and Baseline Comparison”).

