## Discussion

### Summaries

This article presents the detailed statistical analysis plan for the ROADMAP study, which is a clustered randomized controlled trial conducted in diverse areas of China with the purpose of testing the effectiveness of a mobile health platform named *Graded Roadmap* on diabetes control.

The clustered randomized controlled trial design is useful for assessing community-based interventions like the ROADMAP study yet requires careful attention to conduct valid analyses. As such, clustering of outcomes was accounted for when designing the study and, as previously mentioned, will be accounted for in the analysis of the study outcomes. In the study design, the intraclass correlation coefficient was estimated to be 0.15 based on our previous ORBIT study. ORBIT recruited patients who were initiating basal insulin treatment at secondary and tertiary hospitals. The intraclass correlation coefficient may differ from that observed in the studied populations in ROADMAP.

To find out the effectiveness and feasibility of the platform in different regions, four strata were covered by ROADMAP. They are economically developed urban areas, economically developed rural areas, economically less-developed urban areas, and economically less-developed rural areas. Although the economic development level (developed vs less-developed) and locality (urban vs rural) have been included in the predetermined subgroup analysis, more detailed descriptions might be needed for the factorial subgroups.

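### Model 1 omits economic development level and locality, which define the four strata; adding them to the primary analysis costs almost nothing

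*SAP article*

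**What the plan says.** General Analysis Principles sets one level of clustering: "Analyses will adjust for clustering at the village level". Under Primary Analyses, model 1 is a log-binomial GEE clustered on community with continuous baseline HbA1c as its only covariate. In Table 2, the footnote on the composite ABC outcome says that no baseline variable is adjusted for at all.

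The two regional factors enter elsewhere. Covariates-Adjusted Analyses describes "further adjusting for the following covariates (model 2): economic development level; locality", plus any listed baseline variable that differs between arms at P<.01. Both factors are also in the imputation model and in the propensity model for intensive versus basic intervention. Each is a subgroup variable, taken one at a time with an interaction.

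On structure, the Discussion (Summaries) says that "four strata were covered by ROADMAP" and forms them by crossing economic level with urban or rural locality. Participant Recruitment and Randomization says that "for each participating province, 6 districts and 6 of its subordinate communities from each district were selected", giving "19,601 participants from 864 communities or villages in 144 districts or counties in 25 provinces". On allocation it says only: "Following the completion of baseline assessments, communities or villages (clusters) were centrally randomized". The one hint of stratified allocation is under Patient Characteristics and Baseline Comparison: "Cluster characteristics will be summarized in stratified and overall randomization groups". District appears in no model.

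**The concern.** The plan treats economic level and locality as relevant to the outcome in three other models and leaves them out of the one that carries the primary conclusion. Two things follow.

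First, no planned analysis estimates the overall effect adjusted for baseline value and strata alone. Model 2 comes closest, but its remaining covariates are chosen by significance tests on the trial's own baseline data, so its content is not fixed in advance.

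Second, outcome differences between strata that baseline HbA1c does not explain stay in the error term. If allocation was balanced within strata, those differences largely cancel from the treatment comparison, but the model's standard error still counts them. The interval is then too wide and the test has a true size below 5%. If allocation ignored the strata, the standard error is correct, and what is lost is only some available precision.

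**Working it through.** **Inputs.** From Sample Size: 40% control rate, 5-point increase, 576 and 288 communities, 19 patients each, ICC 0.15, two-sided α of .05, stated power 89%. From Participant Recruitment and Randomization: 864 communities in 144 districts, six each. The share s of the ICC that adjustment would remove is not given, so it is an assumption shown as a range.

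**1. The plan's figure.** Design effect = 1 + 18 × 0.15 = 3.70. SE of the risk difference = √[3.70 × (0.40 × 0.60/5,472 + 0.45 × 0.55/10,944)] = 1.57 points. Power = Φ(5/1.568 − 1.96) = Φ(1.23) = 89.0% (88.8% with pooled variance). The stated 89% reproduces from community clustering alone.

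**2. Removing a share s.** The variance of a community mean is proportional to 0.15 + 0.85/19 = 0.1947 without adjustment and to 0.1947 − 0.15s with it. The ratio of adjusted to unadjusted SE is R = √[(0.1947 − 0.15s)/0.1947]. If allocation was balanced within the adjusted groups and the effect is constant, the true size of the unadjusted test is 2[1 − Φ(1.96/R)].

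| Share s | Adjusted SE (points) | 95% half-width | Power, adjusted | Unadjusted test if balanced: size | Unadjusted test if balanced: power |
|---|---|---|---|---|---|
| 0% | 1.57 | 3.07 | 89.0% | 5.0% | 89.0% |
| 10% | 1.51 | 2.95 | 91.3% | 4.1% | 89.9% |
| 25% | 1.41 | 2.76 | 94.4% | 2.9% | 91.4% |
| 50% | 1.23 | 2.41 | 98.2% | 1.2% | 94.1% |

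The adjusted columns take no account of any loss from uneven allocation, which is step 3. None of the figures takes credit for baseline HbA1c, so s should be read as the share left after that adjustment.

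**3. Cost of adjusting if allocation ignored the groups.** With G groups, chance imbalance between arms multiplies the SE by about √[863/(864 − G)].
- Four strata: √(863/860) = 1.002. The gain exceeds this cost once s is above (1 − 860/863)/(0.15/0.1947) ≈ 0.5% of the ICC.
- 144 districts: √(863/720) = 1.095, close to √(6/5). At s = 0 the SE rises from 1.57 to 1.72.

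**4. Simulation at district level** (144 districts of six communities, null effect, 2,000 runs per scenario; the reported unadjusted SE is 1.57 throughout).
- With 4:2 allocation in every district, the true SD is 1.39 at s = 25% and 1.26 at 50%; type I error is 2.5% and 1.3%.
- With unrestricted allocation, the true SD is 1.56 and 1.61, and type I error is 5.2% and 5.6%, so the unadjusted interval is correctly sized. District fixed effects then give SEs of 1.72, 1.55 and 1.35 at s = 0%, 25% and 50%.

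**The case against.** The strongest defence is that no planned property fails. Clustering is handled at the unit of randomization, the 89% power takes no credit for stratification, and under balanced allocation any error in size is conservative. Both factors are in a prespecified model 2. All of this stands, and it limits the point to precision and to a cleanly specified primary estimate.

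The sizes are also hypothetical. The Discussion itself warns that the ICC of 0.15 comes from a hospital-based registry of patients starting basal insulin and may differ here. Baseline HbA1c may already absorb much of the regional difference. This stands too, and is why the table is a range that includes zero.

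A reader might go further and infer that the primary interval is wider than the design warrants, and that district must go into model 1. The documents do not support either.
- The article does not say that allocation was stratified or blocked. Four strata being covered may describe only where communities were sampled. Totals of 576 and 288 fit 4:2 in each of 144 districts (4 × 144 and 2 × 144) but do not prove it.
- Without balanced allocation, district fixed effects gain little at a 25% share (1.55 against 1.57) and lose precision at 0% (1.72).
- Study Overview puts a district or county doctor on each service team, so the effect may vary by district. Under 4:2 allocation, if the between-district variance of the effect were twice that of the outcome level, the community-only SE would be too small for inference to a wider set of districts: 0.92 of the true SE at s = 25% and 0.88 at 50%.
- About 143 district parameters in a log-binomial fit invite non-convergence, which would push the primary analysis onto the plan's fallback methods.

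**Conclusion.** The point holds as an inexpensive improvement to the primary model. Model 1 leaves out the two factors that define the strata, and the only overall estimate adjusted for both may also carry covariates selected from the data. If allocation was balanced within strata, the primary SE is somewhat too large and the test conservative. If it was not, the interval is valid and adjustment can still help.

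The amount cannot be fixed from the article. It runs from nothing at a 0% share to an interval about 4% narrower at 10% and 10% narrower at 25%, assuming ICC 0.15, 19 patients per community, a constant effect, and a share counted after baseline HbA1c. Under those assumptions there is no inflation of false positives, and the planned power stands.

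**What to change.** Add economic development level and locality, or the four-level stratum, to model 1 for all outcomes, including the composite that now has no baseline covariate. Keep community as the GEE cluster with robust standard errors. State which factors, if any, were used in the randomization.

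Account for district in the primary model only if communities were allocated within district, and then in a conditional or random-effect form, or another that does not force about 143 fixed effects into a log-binomial fit. Otherwise confine district to a sensitivity analysis, for example with district-level robust standard errors, and tabulate the ICC at district level beside the community one.

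The cost is a change of SAP wording and two or three parameters against 864 clusters. The plan already uses both factors, so no new data are needed. If allocation ignored the strata, the worst-case loss is about 0.2% of the SE.
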